#### Statistical models to assess the question of whether the quality of life (WHODAS 2.0) and leisure-time physical activity (LTPM) are associated with IC

A slope coefficient of IC (Y = 1 if DIC = 1 or more declines, and Y = 0 if DIC = no decline) will be estimated by a logistic regression model as a function of QoL at baseline (WHODAS = 0 (high), WHODAS = 1 (medium), or WHODAS = 2 (low)) adjusted for the influence of other individual factors such as sociodemographic factors (age, sex, education, and health coverage), comorbidities, loss of ADL/IADL, and socioecological factors (e.g., sociability). The set of V and W will be a collection of covariates similar to previous models, repositioning X = 1 for LTPA that reaches the recommended levels and X = 0 for LTPA that does not reach recommended levels and keeping the same collection of V and W. The relationship between LTPA and IC (or DIC), adjusted for other individual socioecological factors, will also be evaluated by logistic regression.

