Second, the change in the ICI value during the follow-up time in the cohort will be measured and referred to as “ICI delta” (∆IC). The ∆IC is calculated as the difference between the ICI measured in the last follow-up wave minus the ICI measure at the baseline (variable with values between 0 and 10). Third, we will consider the presence of a decline in IC (DIC) if one or more declines in an IC domain are found from the baseline measure. As an example of IC domain decline in the cognitive dimension, a Montreal Cognitive Assessment (MoCA) score of 22 at follow-up versus 27.0 at baseline is considered a decline and probable “dementia” (Nasreddine et al., 2005). The opposite will be classified as no decline.

Finally, a weighted measure of IC (WIC) will be derived from the multivariate regression result of the association between IC subdomains and IADL loss, which will be adjusted for individual sociodemographic factors (see the Analysis section below for detailed description of WIC).

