## Research questions and hypotheses to test

This proposed research will answer three scientific questions:1. Whether IC will decrease as expected at the 3-year follow-up (ICI at end-time ≤ ICI at baseline, or ∆IC < 0), regardless of the socioecological context, individual sociodemographic, behavioral, and clinical factors, and comorbidities (Charlson et al., 1987). This research will statistically test the hypothesis that ICI will not change over time (i.e., follow up IC = baseline IC, or ∆IC = 0).2. If DIC (or TIC) at baseline will be a strong predictor of FA, such as ADL (Mlinac and Feng, 2016), IADL (Hokoishi et al., 2001), falls (Kitcharanant et al., 2020), and death, regardless of the socioecological context, individual sociodemographic, behavioral, and clinical factors, and comorbidities (Charlson et al., 1987). That is, whether the proportion of these ADL/IADL losses, falls, and deaths will be greater in the decline group (e.g., DIC present) than in the unexposed group (e.g., DIC absent). Research will statistically test the hypothesis that there is no association between IC and ADL (or IADL) (e.g., relative risk for TIC or DIC and IADL = 1).3. Whether IC and its five domains are directly associated with a measure of QoL (i.e., World Health Organization Disability Assessment Schedule 2.0 (WHODAS 2.0)) (Prüss-Ustün et al., 2017) and LTPA (i.e., the International Physical Activity Questionnaire (IPAQ)) (Craig et al., 2003), regardless of the socioecological context, individual sociodemographic, behavioral, and clinical factors, and comorbidities (Charlson et al., 1987). Research will statistically test the hypothesis that there is no association between IC and either QoL or LTPA (e.g., relative risk for TIC or DIC and LTPA = 1).

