In contrast, we should also be able to model Y as ∆IC (ordinal variable with values from 0 to 10) as a function of a main vector X (IADL, falls, or death) and a collection of parameters V and W similar to the previous model, but using a multivariate ordinal regression model with a latent variable specification, where composite probability methods are applied to estimate model parameters (Hirk et al., 2019).

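### Question 3 asks about all five IC domains, but the quality-of-life model pools them into one any-decline flag on a three-code WHODAS and gives no result for any domain

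*Protocol article*

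**What the plan says.** All references are to the Protocol article.

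- **The question.** Under Research questions and hypotheses to test, question 3 begins: "Whether IC and its five domains are directly associated with a measure of QoL". It then extends the question to LTPA. The null hypothesis that follows is narrower. It refers to IC as a whole and gives an example, "e.g., relative risk for TIC or DIC and LTPA = 1".
- **The QoL model.** The section on WHODAS 2.0 and leisure-time physical activity specifies a logistic regression: "A slope coefficient of IC (Y = 1 if DIC = 1 or more declines, and Y = 0 if DIC = no decline", estimated "as a function of QoL at baseline (WHODAS = 0 (high), WHODAS = 1 (medium), or WHODAS = 2 (low".
- **The flag.** Under Explanatory variables: IC composite index (ICI), "we will consider the presence of a decline in IC (DIC) if one or more declines in an IC domain are found" relative to baseline.
- **The LTPA model.** "The relationship between LTPA and IC (or DIC), adjusted for other individual socioecological factors, will also be evaluated by logistic regression". LTPA enters as a binary variable, recommended level reached or not.
- **A fuller scale elsewhere.** The section on IC as a predictor of ADLs/IADLs, falls and death treats the change in ICI as an "ordinal variable with values from 0 to 10". There the main explanatory variables are IADL, falls or death, not WHODAS or LTPA.

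**The concern.** The question and the model do not match. The any-decline flag takes the same value whether one domain worsened or all five did, and it does not record which. Its coefficient therefore cannot say whether QoL goes with, for example, cognitive rather than sensory decline, although the question asks about each domain.

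There is also a cost in precision. The outcome is cut to two values and the WHODAS score to three, although domain scores and the index will exist at both waves and WHODAS is collected. At stake are the domain-level answers and, for weak associations, the chance of seeing any association at all.

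**Working it through.** **1. Is there a domain result anywhere for question 3?**

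| Place | Outcome | Main explanatory variable | Domain result? |
|---|---|---|---|
| Question 3, question sentence | IC and each of five domains | QoL, LTPA | Asked for |
| Question 3, null hypothesis | IC (TIC or DIC as examples) | QoL, LTPA | No |
| QoL model | DIC, any domain | WHODAS, 3 codes | No |
| LTPA model | IC or DIC | LTPA, 2 codes | No |
| Ordinal model | Change in ICI | IADL, falls or death | No, and not question 3 |

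The Data analysis section mentions the five domains as an aim of adjustment but gives no model for them.

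**2. The plan's own figures.** No power or sample size is given for question 3. The nearest figure is Table 1, average risk ratio: p0 = 0.0495, p1 = 1.91 × 0.0495 = 0.0945.
n = (1.960 + 0.842)² × [p0(1−p0) + p1(1−p1)] / (p1−p0)² = 514 per group, as stated. This fits a two-sided 5% level, which is used below. Analysed N: 5,500 × 0.85 = 4,675.

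**3. Information kept by the coding.** Assumptions, since the article gives none: normal latent scores for WHODAS and for change in IC; DIC prevalence p of 30–90%; WHODAS in thirds or split 70/20/10.

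- Binary outcome: e_Y = φ(z_p)² / [p(1−p)]. This is 0.637 at p = 50%, 0.576 at 30% or 70%, and 0.342 at 90%.
- Three codes: e_X = squared correlation of the code with the latent score. For thirds, (2 × φ(0.431))² / (2/3) = 0.793. For 70/20/10, 0.622.
- Product for thirds: 0.342 × 0.793 = 0.27 up to 0.637 × 0.793 = 0.51.
- Product for 70/20/10: 0.342 × 0.622 = 0.21 up to 0.637 × 0.622 = 0.40.

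**4. What that does to power.** Power = Φ(√e × δ − 1.960). A full-information test with 80% power has δ = 2.802. With e = 0.51, power is 51%; with e = 0.27, 31%. The 70/20/10 split gives 25–42%. By true latent correlation at N = 4,675 (δ ≈ r√N):

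| r | Uncut scales | Planned coding, both splits, p 30–90% |
|---|---|---|
| 0.03 | 54% | 16–31% |
| 0.05 | 93% | 35–68% |
| 0.07 | 99.8% | 60–93% |
| 0.10 | about 100% | 88–99.8% |

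**5. An association in one domain only.** Simulation: N = 4,675, 400 replicates, five domains with correlation 0.3, and 10%, 20% or 30% of participants declining in each domain. Standardised WHODAS has a slope of 0.08 on latent change in one domain and none in the others.

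| Analysis | Power |
|---|---|
| Any-decline flag, three-code WHODAS | 13–17% |
| Summed change in IC, continuous WHODAS | 32–34% |
| Decline flag for that domain, three-code WHODAS | 82–96% |

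Restoring the full scale helps, but only a domain model recovers this association.

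**6. Equal associations in all five domains.** With the same correlation of 0.3 and a slope of 0.02 per domain, power falls from 44–51% (summed change, continuous WHODAS) to 20–26% (planned coding). At a slope of 0.08, both rows show 100%.

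**The case against.** An odds ratio for any decline is a legitimate and readable summary, and preferring a continuous outcome is often a matter of taste. With some 4,700 people analysed, the planned test still detects an association of r = 0.10 with at least 88% power. That stands, and it limits the precision point to weak associations.

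Several stronger readings are tempting but unsupported:

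- *Power halves.* This is not a property of the plan. The article gives no question 3 effect size, no prevalence of decline and no WHODAS distribution. Halving occurs only where the uncut test has roughly 50–80% power, near r = 0.03–0.04 at this N.
- *The hypothesis names five domains.* It does not. Only the question sentence does.
- *All of question 3 rests on the any-decline flag.* The LTPA model allows IC or DIC, and LTPA is binary, so the WHODAS coding point does not apply there. The missing domain result does.
- *The WHODAS cut-points are missing.* Exact cuts are what a condensed article leaves to a fuller document.

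A further objection concerns the remedy. WHODAS measures disability and is likely to be correlated with baseline IC, which is measured with error. A simulation with a WHODAS–baseline correlation of 0.1–0.2, reliability of 0.8–0.9 and no WHODAS effect on latent change illustrates the problem. Follow-up ICI adjusted for baseline ICI rejected the null in 37–95% of runs, and the planned logistic model without baseline IC in 53–99.5%. This does not favour the plan, but the remedy needs a sensitivity analysis.

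Nor can the gap be put down to condensation. The article itself fixes the outcome, the coding and the model type.

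**Conclusion.** The concern holds in a limited form. Followed as written, the question 3 section gives no result for any domain, although the question asks about all five. This follows from the text alone.

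The loss of information is real, but its size rests on assumptions: 27–51% kept with WHODAS in thirds, or 21–40% with a 70/20/10 split, for normal latent scores and 30–90% declining. It matters greatly for r of about 0.03–0.05 and little at 0.10 or above. The one-domain contrast (13–17% against 82–96%) likewise depends on the simulated slope and correlation. A reader might infer one headline power loss; the article does not support one. This is an inexpensive improvement rather than a fatal flaw.

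**What to change.** In the section on WHODAS 2.0 and leisure-time physical activity:

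1. Add one model per domain, with the domain score or domain decline as outcome, for WHODAS and for LTPA, with a stated multiplicity correction.
2. For QoL, enter the WHODAS score uncut and use a full-scale IC outcome. Choose either follow-up ICI adjusted for baseline ICI or change in ICI as the main analysis, and report the other as a sensitivity analysis.
3. Keep the logistic any-decline model as secondary. LTPA may stay binary.

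Reconcile the scoring first. ICI is said to run from 0 to 14, but five domains coded 0–2 sum to at most 5 × 2 = 10, and its change is given as 0 to 10. A difference must also be able to take either sign. The vitality rule codes sums of 0, 2–4 and 5–6 but gives no code for a sum of 1.

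The cost is analysis wording, five extra models per exposure, and a slope less simple to explain than an odds ratio. No new data are needed, and the article states that none have yet been collected.

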### Explanatory variables: IC composite index (ICI)

An IC composite score or index (IC index or ICI) will first be created, as suggested by Gutiérrez-Robledo et al. (2019). This score aims to express a summary measure of impairments for an older adult. Initially, each continuous or ordinal subdomain measure will be dichotomized based on acceptable cut-off points to create a binary variable of 0 or 1 (see Table 3 for cutoff points across all subdomain measures). Within a domain, the values of these recoded subdomain measures will be summed up to create a “subdomain score.” The subdomain scores will range from 0 to 2 for the four subdomains with only two measures and from 0 to 6 for the subdomain with six measures (i.e., vitality). Then, each domain of the five IC components will be subdivided into three categories based on the sum of the scores of its subdomains, with the following numerical score: no impairment = 0, mild impairment = 1, and severe impairment = 2. For example, the four domains with only two subdomain measures (e.g., cognitive with subdomain measures memory and cognitive) will be coded 0 if their subdomain score (sum of their subdomain measure) is 0, 1 if the subdomain score value is 1, and 2 if the subdomain score value is 2. The domain with six subdomain measures, vitality (subdomains comorbidity, medication, biomarkers, pain, strength, and nutrition), will be coded 0 if its subdomain score is 0, 1 if the subdomain score is 2–4, and 2 if the subdomain score is 5–6. Scores for each of the five domains will be summed up to produce a composite IC index ranging from 0 (best possible ICI) to 14 (worst possible ICI).

Subsequently, this baseline ICI will be classified in four ways. First, using the terciles of ICI (TIC), ICI values less than or equal to the first tercile (Q1) will be classified as low TIC; ICI values between Q1 and the third tercile (Q3), including Q3, will be classified as medium TIC; and ICI values above Q3 will be classified as high TIC. This analysis model is explicitly shown in Figure 1.

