#### Statistical models to assess whether IC is a predictor of ADLs/IADLs, falls, and death

Two Cox regression models will be evaluated to estimate the incidence rates of outcomes (i.e., functional loss measured by IADLs, falls, and death) associated with IC at baseline (e.g., TIC, DIC, and WIC) (ElHafeez et al., 2021). Cox’s first model has the indicator variable X to denote the association with each of the two groups of IC exposure at baseline (e.g., X1 = 1 for medium and high TIC and X1 = 0 for low TIC), with Y being the adverse incident at 3 years of follow-up (loss of ADLs/IADLs, falls, and death); survival times will be measured by the interval from the first assessment to the adverse incident. For subjects who do not experience an adverse incident, the follow-up time will be the last evaluation of the study.

The model also comprises a collection of covariates V with the potential to be a confounding factor in the association between Y and X (e.g., sociodemographic factors), and W would be the potentially interactive term between X and V (e.g., sex * TIC). The regression coefficient of X describes the effect of TIC on outcome Y, that is, the risk of greater or lesser loss of ADL/IADL, falls, and death for those exposed to medium or high TIC relative to those exposed to low TIC. The W terms will assess whether there is a positive interaction between TIC and one of the V confounders that have been identified to be potentially interacting. The model will extend by substituting TIC for DIC or WIC as the main exposure variable X. Alternatively, we can also model Y (e.g., IADL) as a function of X (either TIC, DIC, or WIC) and the same set of V and W using logistic regression to estimate the odds ratio of the outcomes.

We will evaluate the IC trajectory through changes in IC scores (∆IC or WIC) or the presence of IC decline (DIC) after 3 years, along with their associations with IADL outcomes, falls, and death. For example, the mean/median of ∆IC (or WIC) and the prevalence of DIC will be generated at baseline and at the end of the 3-year follow-up. We will then generate the mean/median or prevalence of IC measure by levels of ADL/IADL, falls, and death. The means/medians of IADLs and the incidence of falls and death after 3 years of follow-up will also be estimated.

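### The models of IC decline on quality of life and physical activity do not name baseline IC as a covariate, although room to decline depends on it

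*Protocol article*

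**What the plan says.** The third research question in the protocol article asks whether IC and its domains are associated with WHODAS 2.0 and with leisure-time physical activity (LTPA), "regardless of the socioecological context, individual sociodemographic, behavioral, and clinical factors, and comorbidities".

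The section on the quality-of-life and LTPA models makes DIC the outcome, coded 1 for one or more declines and 0 for none. The exposure is baseline WHODAS in three levels. That model is "adjusted for the influence of other individual factors such as sociodemographic factors (age, sex, education, and health coverage), comorbidities, loss of ADL/IADL, and socioecological factors". The exposure is then replaced by LTPA (recommended level reached or not), "keeping the same collection of V and W". V was introduced in the preceding modelling section as "a collection of covariates V with the potential to be a confounding factor". None of these places names baseline ICI, its terciles or the baseline domain scores.

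The section on the IC composite index defines the outcome: "we will consider the presence of a decline in IC (DIC) if one or more declines in an IC domain are found from the baseline". It scores each domain as "no impairment = 0, mild impairment = 1, and severe impairment = 2", from items that Table 3 codes 0 or 1.

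**The concern.** DIC is a worsening from baseline on a bounded scale. A domain already at 2 cannot worsen, yet it is counted as not declined. An item already impaired can only stay impaired or recover. The chance of DIC therefore falls as baseline impairment rises, even when nothing else differs between participants.

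If people with poor WHODAS or low activity start with more impairment, the exposure coefficient partly measures how much capacity was left to lose. The third research question could then return a null or inverted answer where there is a modest adverse association.

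The covariates that are named do not stand in for baseline IC. Comorbidity count is one of the 14 items in Table 3. The Eligibility section aims to enrol people without significant ADL or IADL loss, so baseline ADL/IADL should vary little. If loss at follow-up is meant, it is a post-baseline variable.

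**Working it through.** The plan gives no figure for these models, so there is none to reproduce. It also gives no item prevalences, onset rates or correlations. All such inputs below are assumptions.

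**1. The mechanism by hand.** Take one two-item domain with independent items, 10% onset per item over follow-up and no recovery.
- Baseline score 0: P(decline) = 1 − 0.9² = 0.19
- Baseline score 1: P(decline) = 0.10
- Baseline score 2: P(decline) = 0

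Now compare two groups with identical onset but baseline item prevalence of 20% and 40%. P(decline) = (1 − p)² × 0.19 + 2p(1 − p) × 0.10.
- p = 0.2: 0.64 × 0.19 + 0.32 × 0.10 = 0.1536
- p = 0.4: 0.36 × 0.19 + 0.48 × 0.10 = 0.1164
- Odds ratio = (0.1164/0.8836) / (0.1536/0.8464) = 0.73

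Within each baseline score the two groups have the same risk. The whole departure from 1 comes from the starting score.

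**2. The full scoring, simulated.** From the protocol: 14 binary items, five domains coded 0/1/2, DIC = any domain worse, CDR item 0 at baseline, comorbidity in the model. Assumed:
- correlation of the exposure with latent IC 0.3 or 0.6
- item prevalence 0.2 or 0.4
- onset 10%; recovery 0 or 20%
- vitality score 1, which the protocol leaves uncoded, set to 0

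With no true effect (correlation 0.6, prevalence 0.4), P(DIC) fell from 0.65 at baseline ICI 0–1 to 0.16 at ICI 8–9.

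**3. No true effect, onset unrelated to latent IC.**
- WHODAS, per step worse: odds ratio 0.75 to 0.93 without baseline IC, 1.01 to 1.04 with baseline ICI. A separate set of runs using the five domain scores gave 0.76 to 0.91 without and 1.00 to 1.03 with.
- LTPA, active against inactive: 1.10 to 1.51 without, 0.95 to 0.99 with baseline ICI.
- False-positive rate for WHODAS with 4,675 analysed (5,500 × 0.85) and no recovery: 48% (correlation 0.3, prevalence 0.2) to 100% (0.6, 0.4) without baseline ICI; 6% to 8% with it. Nominal level 5%.

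**4. A true effect is present.** Sixteen scenarios for each exposure, half of them with onset rising with low latent IC.
- WHODAS, item odds ratio 1.1: the sign reversed without baseline ICI in 5 of 16 (down to 0.84, against 1.15 with it).
- WHODAS, item odds ratio 1.3: 0 of 16 reversed. The most attenuated estimate was 1.00, against 1.46 with baseline ICI.
- LTPA, protective effect of the same sizes: the odds ratio crossed above 1 in 7 of 16 and 2 of 16.

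**5. No true effect, but low latent IC itself raises onset.**
- Log-odds 0.3 per SD: WHODAS odds ratio 1.03 to 1.19 with baseline ICI. For LTPA, 0.86 to 1.13 without and 0.77 to 0.94 with.
- Log-odds 0.3 to 0.5 per SD, five domain scores: WHODAS 0.93 to 1.17 without, 1.06 to 1.25 with.
- In a further set at 0.3 per SD (4,675 analysed, 60 runs per cell), the domain-adjusted model showed significant harm in 20% to 97% of runs. The unadjusted model showed significant protection in 0% to 17% of runs in seven of eight cells and 65% in the other.

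**The case against.** **The lists are open.** The WHODAS list is introduced by way of example, V is defined loosely, and the Discussion promises to include the most relevant risk factors for IC. A reader might infer that the protocol excludes baseline IC. It does not; it fails to name it, and a fuller analysis plan could add it. Clinical factors, which the research question mentions, could also take in some items such as pain or medications. What stands is that an analyst following the categories as written would fit the model without baseline IC.

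**The bias may be small or absent.** If low IC speeds decline, as the Rationale suggests it might, the unadjusted estimate can sit near 1. This is correct, but that result comes from two biases offsetting each other, by an amount nobody can know in advance.

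**Adjustment is not a cure.** Baseline IC is measured with error and at the same time as the exposure. Step 5 shows that the adjusted model can report harm that is not there. This stands in full and limits what the fix can claim.

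**The ceiling may be weaker than simulated.** The protocol's one example of decline is a MoCA change from 27 to 22. It may mean raw scores, although it also crosses the cut-off of 25. Eligibility narrows the baseline spread, and Table 3 as written gives the point to stronger grip, which runs against the assumed direction for that item. These reduce the size of the effect; regression to the mean remains.

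**The ∆IC model.** A reader might extend the point to the ordinal model of ∆IC, which uses "a collection of parameters V and W similar to the previous model". The documents do not support that step. The exposures there are IADL, falls or death, ∆IC is undefined for those who die, the model is offered only as a possibility, and none of the results above use those exposures.

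**Conclusion.** The point holds for the DIC models on WHODAS and on LTPA, as a matter of what is not named. Because domains are capped at 2, leaving baseline IC out pulls the estimate towards poor quality of life or inactivity seeming protective, wherever these go with worse baseline IC. With onset unrelated to latent IC the null odds ratio is about 0.75 to 0.93 per WHODAS step.

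A reader might infer that reversed results are to be expected. The results do not support that: reversal needs a weak true effect together with favourable conditions, and at an item odds ratio of 1.3 the main consequence is attenuation. Nor is the adjusted model unbiased; its null odds ratio is about 1.03 to 1.25 if low IC itself speeds decline. Direction follows from the scoring plus the assumed exposure–IC association. Every size rests on inputs that the documents do not give.

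**What to change.** In the section on the quality-of-life and LTPA models:
- name the five baseline domain scores, as categories, among the covariates of every DIC model;
- restrict any domain-specific analysis of decline to participants whose baseline score in that domain is below 2;
- report the model without baseline IC beside the adjusted one, and state that a conclusion rests on both, since the first is pulled towards protection by the ceiling and the second can keep residual confounding towards harm.

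The cost is wording only. The baseline scores are already to be collected from everyone, and the article states that no data have yet been gathered. The adjusted estimate becomes conditional on baseline IC and inherits its measurement error, which should be said when results are reported.
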